### Interventions

#### TCM Guizhi-Shaoyao-Zhimu decoction preparations and placebo preparation

Traditional Chinese medicine decoctions are made by boiling herbs in boiling water for hours. However, for the convenience of administration, handling, distribution, and storage, Guizhi-Shaoyao-Zhimu decoction and placebo granules will be distributed to the participants. The preparation of Guizhi decoction and placebo will be entrusted to Jiangsu Tianyin Pharmaceutical Co, Ltd., and all operations will strictly follow the procedures stipulated in the Chinese National Pharmacopoeia. The placebo is composed of starch, dextrin, and bitters, and its smell and taste are similar to those of traditional Chinese medicine granules. The composition and function of all herbs in Guizhi decoction are summarized in Table 2.

**Table 2 Tab2:** Composition and action of Guizhi-Shaoyao-Zhimu decoction in Chinese herbal medicine

Ingredient	Granule dose	Action (TCM)
*Cinnamomum cassia* (guizhi)	4.5 g	1. Relieving exterior syndrome by diaphoresis 2. Harmonizing yingfen and weifen 3. Warming the channel and activating blood circulation warming the meridian to relieve pain
Radix of *Paeonia lactiflora* (Shaoyao)	4.5 g	1. Nourishing the blood 2. Reducing yin 3. Soothing the liver 4. Relieving pain stabilizing yin and yang in the liver
Radix and Rhizoma of *Glycyrrhiza uralensis* (gancao)	3 g	1. Clearing heat and removing toxicity 2. Invigorating spleen and supplementing qi moderating the property of herbs
Rhizoma of *Anemarrhena asphodeloides* (Zhimu)	4.5 g	1. Clearing heat-fire nourishing yin for moistening dryness
Rhizoma of *Atractylodes macrocephala* (Baizhu)	4.5 g	1. Invigorating the spleen replenish qi
Rhizoma of *Zingiber officinale* (Shengjiang)	3 g	Resolve the exterior and dissipate cold
Radix of *Saposhnikovia divaricata* (Fangfeng)	4.5 g	1. Expelling wind to relieve superficies 2. Removing dampness to relieve pain
Processed lateralis Radix of *Aconitum carmichaeli* (Paofuzhi)	1.5 g	1. Tonifying fire and helping yang 2. Dispelling cold and removing dampness

#### Conventional Western medicine preparation

For methotrexate tablets, specification was as follows: 2.5 mg × 16 tablets/bottle; manufacturer: Shanghai Xinyi Pharmaceutical Co., Ltd.; national drug approval number H31020644.

For folic acid tablets, it was as follows: 5 mg × 100 tablets/bottle; manufacturer, Shanghai Xinyi Huanghe Pharmaceutical Co., Ltd.; national drug approval number H31020147.

#### Medication method

For the experimental group (Western medicine + Guizhi-Shaoyao-Zhimu decoction), Guizhi-Shaoyao-Zhimu decoction will be taken twice a day (30 g each time). Combined MTX will be taken orally once a week (10~15 mg). Folic acid tablets will be taken orally twice a week (5 mg).

For the control group (Western medicine + TCM placebo), TCM placebo twice a day, 30 g each time. MTX is taken orally 10~15 mg once a week. Folic acid tablets should be taken 5 mg orally twice a week.

Each patient lasted for 3 months.

#### Combination of drugs

For combination of drugs, according to ethical requirements, if the patient’s pain is unbearable and the doctor considers it necessary to add other drugs to the regimen, drug combinations can be used. The combination of drugs is limited to nonsteroidal anti-inflammatory drugs and low-dose hormones. The dosage and starting and ending time will be recorded in detail.

### Measurement items and time points of data collection

#### Outcome measure

##### General information (before treatment)

The patients’ general information, including demographic data, general medical examination items, and general clinical data will be collected at baseline.
Demographic data: The patients’ name, sex, age, nationality, occupation ID number, date of birth, home address, and contact information will be collected.General medical examination items will include respiration, body temperature, pulse, blood pressure, tongue coating, and pulse measurements.General clinical data will include history of present illness, past medical history, family history, personal life history, menstrual history, marital history, allergy history, and social history.

##### Outcome variables

The primary outcome of this trial will be recorded at baseline and at weeks 1, 2, and 3.
Laboratory indexes including routine blood examination, ESR, CRP, and hepatic and renal function will be measured.*The visual analog scale (VAS)* [13]. The pain VAS is self-completed by the respondent. Using a ruler, the score is determined by measuring the distance (mm) on the 10–cm line between the “no pain” anchor and the patient’s pain anchor, providing a range of scores from 0 to 100 [14, 15]. A higher score indicates greater pain intensity.*Disease Activity Score in 28 joints-Erythrocyte Sedimentation Rate (DAS28-ESR)*. DAS28-ESR was calculated as 0.56 × √(Tender joint count) + 0.28 × √(Swollen joint count) + 0.7 × ln ESR + 0.014 × VAS-GH [16].*Measurement scale for TCM symptoms*. To facilitate the evaluation of the results, we will use the measurement scale for TCM symptoms recommended by the Guidelines for Clinical Research of Chinese Medicine (New Drug) [12] to score the symptoms of the patients. The scale consists of 4 major symptoms and 7 minor symptoms. Each symptom is graded on 4 levels, ranging from zero, mild, medium, to severe, with corresponding scores of 0, 1, 2, and 3. The total score was calculated by adding up each score in the scale and using these scores to calculate an efficacy indicator (EI) for the evaluation of treatment efficacy.

EI = (Total symptom score at baseline − Total symptom score post-treatment)/Total symptom score at baseline × 100%

The degree of symptom improvement will be presented in four categories ranging from full recovery (EI ≥ 90%), good recovery (90% > EI ≥ 70%), modest recovery (70% > EI ≥ 30%) to no recovery (EI < 30%).
5.*Ultrasonic assessment*. The 7-joint ultrasound score (US7) [17] is used to determine the degree of synovitis, synovial hyperplasia, and bone erosion. This score examines 7 joints (wrist, MCP2, MCP3, PIP2, PIP3, MTP2, and MTP5 joints) of the clinically dominant hand and foot of the patients. The synovitis, tenosynovitis, and bone erosion of each joint will be observed, with the highest score being 94 points according to the following standards.
Synovial thickening is graded on four grades according to no, light, medium, and heavy, and the corresponding scores are 0, 1, 2, and 3.
I*0 points*. No synovial thickeningII*1 point*. Mild synovial thickening (the thickened synovium is located only in the circumferential triangle of the bone)III*2 point*. Moderate synovial thickening (thickened synovial membrane extending from the circumferential triangle to the middle but not to the epiphysis)IV*3 points*. Severe synovial thickening (thickened synovial membrane extending from the circumferential triangle to the middle and metaphysis)Synovitis of tenosynovitis is graded on two grades according to no or have, and the corresponding score is 0 and 1.
I*0 points*. No hypoechoic thickened tissue with fluid and Doppler flow signal in the tendon sheathII*1 point*. Hypoechoic thickened tissue with fluid and Doppler flow signal in the tendon sheathBone erosion scored 0 or 1 on a no or yes basis.
I*0 points*. Continuous absence of cortical bone defectsII*1 point*. Cortical discontinuity in the joint cavity in two vertical planesSynovitis. If synovial thickening is present, a color Doppler flow signal (PDUS) is additionally observed with color Doppler. The pulse repetition frequency (PRF) is set to a minimum of 0.7 to 1.0 KHz. The Doppler flow signal is graded on 3 levels.
I*0 points*. No blood flow signalII*1 point (mild)*. A small amount of pitting blood flow signal.III*2 points (moderate)*. A continuous blood flow signal covering less than 50% of the joint cavity.IV*3 points (severe)*. The area of blood flow signal exceeds 50% of the joint cavity

### Safety guarantee and evaluation

All trial interventions will be conducted under the guidance of rheumatology experts. The researchers will closely observe the physical conditions of the participants. Routine hematuria and liver and kidney function tests will be performed before enrollment and at 1, 2, and 3 months after enrollment. Adverse events and serious adverse events will be recorded by all participants and will be reported to the principal investigator and professional leader in the event of adverse events to find a reasonable solution. Conduct monthly internal team review of adverse events related to drug use. In addition, the safety and efficacy of the intervention will be examined by two clinicians and statisticians independent of the trial, who will also make professional recommendations on the pace of trial recruitment, whether to continue and terminate the trial, and, if necessary, on amendments to the protocol. Subjects have the right to withdraw their consent to participate in the study at any time for any reason, without any consequences for further treatment.

### Sequence generation and allocation concealment mechanism

Use the online central random system of the Chinese Academy of Chinese Medical Sciences. The drug will be randomly coded according to the clinical trial randomization protocol and used as the subject’s unique identification code. Subjects are included in a certain order, and random numbers can be obtained online. Subjects are randomly assigned to the experimental group and the placebo group in a 1:1 ratio. A double-blind and placebo-controlled trial design is adopted. The patients are randomly assigned drug A or B, respectively, and sequenced according to maintain blinding. Subjects and researchers are blinded, and drug A and drug B are distributed in the order in which patients visit the clinic. If serious adverse events occur during the test, the emergency envelope should be unsealed immediately and delivered to the researcher of the research unit for storage. A double unblinding method will be used. At the end of the study, after verification of blinding, the data will be locked, and the statistical specialist who maintains the blinding will unblind the first level. Statistical experts will be informed of A/B group assignments corresponding to each case number for statistical analysis of all the data. When the statistical analysis and the summary report are completed, level II unblinding will be conducted at the clinical summary meeting to reveal the subjects in group A and group B.

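### The emergency envelope is opened at every serious adverse event and passed to a blinded role, and the text does not settle whether one opening exposes one patient or many.

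*Protocol article*

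**What the plan says.** All the relevant statements stand in one section of the Protocol article, *Sequence generation and allocation concealment mechanism*.

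- **Trigger.** "If serious adverse events occur during the test, the emergency envelope should be unsealed immediately". Nothing is said about relatedness, about whether anyone needs the allocation, or about who decides.
- **Recipient.** The opened envelope is to be "delivered to the researcher of the research unit for storage".
- **Who is blind, and what is handed out.** "Subjects and researchers are blinded, and drug A and drug B are distributed in the order in which patients visit the clinic".
- **Assignment.** "The patients are randomly assigned drug A or B".
- **Unique code.** "The drug will be randomly coded according to the clinical trial randomization protocol and used as the subject’s unique identification code". Random numbers come from a central online system.
- **Two-level unblinding.** After data lock, "Statistical experts will be informed of A/B group assignments corresponding to each case number for statistical analysis of all the data". What A and B stand for is disclosed only once the analysis and report are finished.

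The section does not say whether the pack shows the letter or the unique code, or whether an envelope holds one subject's arm or the key to the letters.

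**The concern.** Two things are fixed badly.

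First, the opening rule is automatic. An SAE that calls for no knowledge of the allocation still breaks the code, and the result goes to a role that the same section lists as blinded. Each such opening is an avoidable loss of blinding.

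Second, how far one opening reaches depends on the labelling, and the labelling text points both ways. With two arms and a visible letter, learning one patient's arm gives the meaning of both letters.

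The outcomes make this matter. Those listed as primary include a self-completed pain VAS, a TCM symptom score, DAS28 (with a tender joint count and a patient-reported global scale) and the 7-joint ultrasound score. The *Discussion* itself names operator dependence as a limitation of ultrasound. All of these can shift with what the patient or the examiner expects.

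**Working it through.** **1. The opening rule against the blinding statement.** The trigger is the occurrence of an SAE, the timing is immediate, and the recipient is the researcher of the unit. The sentence just before it keeps researchers blind. Both cannot hold for the same person once an opened envelope is delivered. The section does not separate a researcher who may see the code from one who may not.

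*The drop out criteria* withdraw patients with serious adverse reactions to the study drugs. An SAE that is not such a reaction also triggers the opening, and that patient may stay in the trial and be assessed afterwards with the code broken.

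**2. The two labelling descriptions side by side.**

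| Description | What it implies at the clinic |
|---|---|
| Unique code per subject; A/B linked to case numbers only after data lock | The letter is hidden until level I unblinding |
| Patients are assigned drug A or B; drug A and drug B are handed out in visit order | The letter may be visible at dispensing |

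Level I unblinding is a meaningful step only if the letters were hidden until then. Handing out drug by letter undoes that.

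**3. Reach of one opening under each reading.**

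| Pack shows | Envelope reveals | Patients exposed by one opening |
|---|---|---|
| A or B | That participant's arm, or the key | Every patient whose letter is known, up to 152 |
| Unique code only | That participant's arm | 1 |

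**4. Chance that the rule is used at all.** The number randomised is 152 (*Sample size calculation*: 122 with a 20% dropout allowance, 122 / 0.80 = 152.5, stated as 152). The documents give no SAE rate, so the risk per patient, r, is an assumption. With independent patients:

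P(at least one opening) = 1 − (1 − r)^152

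Expected number of patients with an SAE = 152 × r

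| Assumed r | Chance of at least one opening | Expected patients with an SAE |
|---|---|---|
| 0.5% | 1 − 0.995^152 = 0.533 | 0.76 |
| 1% | 1 − 0.99^152 = 0.783 | 1.52 |
| 2% | 1 − 0.98^152 = 0.954 | 3.04 |

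Under the favourable reading in step 3, the last column is also the expected number of patients unblinded. The middle column is the chance that the rule is triggered at least once. It is not the chance that all 152 patients are unblinded.

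**The case against.** The best defence is that A and B are shorthand for the two arms. The section gives each subject a unique drug code and links letters to case numbers only after lock, which makes most sense if the site never sees a letter. The contents of the envelope and the pack label are also details that an article may leave to the full protocol. This stands as far as it goes: exposure of many patients is a possible reading and not an established one. It does not remove the sentence that has drug A and drug B handed out at the clinic.

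It can also be said that the envelope goes to the researcher only for storage, that nothing makes this person an outcome assessor, and that the note to Table 1 provides for assessors blinded to the randomisation. This limits the harm. It does not explain why an opened code should go to a blinded role, or why it should be opened when nobody needs it.

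A reader might infer two stronger conclusions, and the documents support neither.

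- *Allocation concealment is lost for patients not yet randomised.* Knowing what A contains does not tell anyone whether the next patient will receive A or B. Allocations come from a central online system, and nothing says that staff can foresee the next letter.
- *The double blind fails for the whole trial.* Outcomes recorded before an opening cannot be biased by it, and a late opening touches few assessments. Wider damage would also need letters visible at dispensing and the knowledge to reach patients or assessors. Neither is stated.

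**Conclusion.** The opening rule is a defect as written, on any reading of the labelling. It breaks the code at every SAE without a need for the allocation, and it sends the result to staff who should stay blind. The labelling text is inconsistent, so the reach of one opening cannot be fixed from the document: one patient if packs carry only the unique code and envelopes are participant-specific, and up to 152 if the letter is visible at dispensing. At least one opening is more likely than not at each assumed SAE risk (53%, 78% and 95% at 0.5%, 1% and 2%). Those figures rest on assumed rates and independent patients.

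This should be corrected.

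**What to change.** Rewrite the section so that its statements agree.

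1. Packs carry only the unique code issued by the central system already in use. No letter appears at the clinic.
2. A/B exists only in the statistician's file until level I unblinding.
3. Each emergency envelope reveals one participant's allocation and nothing more.
4. Automatic opening at every SAE is replaced by opening when the allocation is needed. Each opening is logged with date, reason and recipient, and is disclosed only to those who need it.
5. Outcome assessors, including the ultrasound examiner, stay blind after any opening.

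The cost is minor labelling work, a short opening procedure with a log, and one revised paragraph. Part of this may already be practice under the unique-code statement, in which case the change is mainly one of wording.

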### Data quality control

A training will be done for all participating staff on the trial protocol, usage of the randomization, data management systems, etc. The principle investigator will supervise the proceed of the trial at least once every month, collecting, assessing, reporting, and managing solicited and spontaneously reported adverse events and other unintended effects of trial interventions or trial conduct. An ethics committee will review conduct especially on safety, rights, and well-being of the participants at the middle and the end of the trial. The auditing will be done by Clinical Evaluation Center of the China Academy of Chinese Medical Sciences at the beginning, middle, and end of the trial.

### Data collection and management

Composition of data monitoring committee (DMC) is composed of professional statisticians. They will perform statistical analysis, participating in the entire process from the research design and implementation to the analysis and summary. A statistical analysis plan will be developed after the completion of the study program and completion of the case reporting forms, and the statistical analysis reports will be provided after the necessary modification of the data analysis is performed as necessary during the research process. According to the project of the case report form, EpiData3.1a software will be used to establish the corresponding entry procedure and set the logical examination qualifications at the time of entry, and the database will be piloted to establish a database system dedicated to this experiment. The signed case report form and the audit statement will be given to the data administrator, who will examine the date, group criteria, culling criteria, shedding criteria, and missing values. If there is doubt about “data question form,” it will be returned to the monitor, and the researcher will answer and sign the question in writing and return it to the data administrator; “data question form” should be properly stored to protect confidentiality before, during, and after the trial. The data are entered synchronously by the data administrator using a two-person entry method. The database will be checked for each item using the verification function in the EpiData3.1a software; any inconsistent result values will be reported. The original case reporting tables will be checked item by item, and 10 case reporting tables and the data in the database will be randomly selected for manual comparison to ensure that the data in the database are consistent with the results in the case reporting tables. The original CRFs and any other records will be archived for 5 years.

### Statistical analysis

An independent statistician will perform statistical analysis according to the statistical analysis plan using SPSS software (version 26; SPSS Inc., Chicago, IL, USA). Continuous variables will be expressed as the mean (standard deviation) if the data are normally distributed; otherwise, they will be expressed as the median (interquartile). Categorical variables will be presented as frequencies (percentages). Baseline analyses will be performed using analysis of variance or nonparametric tests for continuous variables, and chi-squared or Fisher’s exact tests for categorical variables, respectively. Changes from baseline to post-treatment in DAS28, VAS, TCM syndrome scores, and US7 will be analyzed using analysis of covariance with associated 95% confidence intervals. A two-sided *P* value of 0.05 or less is considered statistically significant. Multiple imputation will be used to handle any missing data.

### Monitoring and audit

An inspector appointed by the sponsor will conduct irregular monitoring visits on site or remotely. At any stage of the trial, auditors can check compliance with the protocol to ensure that no violations of basic principles of clinical practice have occurred. In addition, the inspector needs to check the accuracy, consistency, and completeness of the test data.

### Trial protocol amendments

The protocol may need to be modified depending on the progress of the trial. If any modification is required, all researchers will work with clinical and statistical experts to fully demonstrate the need for improvement before making any modification.

### Dissemination

The study results will be disseminated in Open Access and peer-reviewed journals and shared through oral and poster presentations at international conferences. All resources will be uploaded to an online knowledge management platform, and the research team will report their individual results to study participants.

## Discussion

According to the clinical manifestations of RA, it is included in the category of arthralgia disease in TCM. During the early stage of the disease, wind chill invades, blood vessels are blocked, Qi-blood transportation in the joints is affected, and veins are blocked, resulting in qi deficiency and blood stasis. As time passes, qi and the blood gradually become weak, becoming unable to nourish muscles and bones and causing local pain; notably, pain is the most difficult of these symptoms to relieve. Later, doctors began to use Guizhi-Shaoyao-Zhimu decoction to treat the disease, and the effect was considerable. In this trial, Chinese herbal granules were used instead of TCM decoction pieces to ensure the quality requirements of Chinese medicine ingredients in terms of drug concentration and efficacy.

The potential mechanism of Guizhi-Shaoyao-Zhimu decoction in the treatment of RA remains to be elucidated. Recent clinical research has shown that the clinical cure rate of Guizhi-Shaoyao-Zhimu decoction for RA patients may be between 87.5 and 95.8%, which is higher than that of indomethacin, tripterygium glycosides, and prednisone [18–20]. In addition to its significant efficacy, Guizhi-Shaoyao-Zhimu decoction has been used in clinical practice for many years, and no obvious adverse reactions have been reported [21]. Studies have shown that [22, 23] Guizhi-Shaoyao-Zhimu decoction can alleviate the progression of RA by inhibiting the differentiation and activities of osteoclasts, reducing the proliferation of synovial cells, and increasing the apoptosis of synovial cells both in vitro and in vivo.

MSUS can reveal the pathological changes that occur during early-stage RA and can be used to assess the activity level of RA patients. MSUS can help guide clinical treatment and has considerable advantages. Therefore, we used MSUS as an important monitoring method for the diagnosis and treatment of RA. After all, MSUS is an inspection method with the advantages of nonionizing radiation, safety, noninvasiveness, and ease of operation.

Based on the current evidence, we designed this double-blinded randomized controlled clinical trial. MSUS is used to evaluate the efficacy and safety treatment with Guizhi-Shaoyao-Zhimu decoction in RA patients. This trial complies with the SPIRIT 2013 [24] and SPIRIT 2013 statement, explanation, and elaboration [25], which covers scientific, ethical, and safety issues (Annex 1). The results of this trial may provide insights into how to improve the clinical symptoms of RA patients. The results of this trial may help to improve their clinical symptoms and to delay further joint destruction. We hope that this trial may provide preliminary evidence for the efficacy of Guizhi-Shaoyao-Zhimu decoction in treating RA patients and that these results aid researchers, practitioners, and patients alike.

There are still some limitations in this study. First, MSUS cannot fully assess the condition of the joint because of its poor of penetration ability. Moreover, MSUS is the imaging examination that is most subjectively affected by the operator. The quality of the ultrasound image depends on the examiner’s experience, the resolution of the instrument, and the placement of the ultrasound probe. On the other hand, there is currently no international uniform standard for MSUS in evaluating RA patients. Second, the study will be conducted in Shanghai, China. It is not certain whether the relative effects of Guizhi-Shaoyao-Zhimu decoction will be similar in other ethnic groups. Third, which components in Guizhi-Shaoyao-Zhimu decoction have an effect on the therapeutic effect requires further research and exploration.

